### Data management

Table 1 outlines the proposed data analysis methods as they correspond to research questions, hypotheses, and outcome measures. Where appropriate, large font showcards will be used by the researcher to visually present answer options for surveys. Most survey responses will be recorded by the researcher in Research Electronic Data Capture (REDCap) [53, 70], an electronic data capture tool hosted by The Research Institute of St. Joe’s Hamilton, which allows for secure online data entry from multiple sites into a central data repository. Some data that is also relevant to the clinical assessments is recorded in TaperMD and later imported into REDCap. These processes were trialed in our feasibility study [42]. The database has automatic checks and warnings for missing data and will have regular checks for missing data and outliers among data for all sites. Clinical and patient characteristic data from TaperMD will also be imported into REDCap. These processes were tested in our feasibility study [42]. No patient identifiers will be entered into either TaperMD or REDCap, both of which are compliant with both federal and provincial Canadian privacy laws. Patient identifiers will be kept strictly confidential; electronic files containing identifiers will be encrypted and password protected and held in a secure network. Paper documents containing patient identifiers will be held in a locked filing cabinet in a locked room accessible only to members of the study team. Electronic and paper documents will be kept for 10 years.

**Table 1 Tab1:** Data analysis plan

Research question	Hypothesis	Outcome measure	Timing	Method of analysis
What is the effect of a structured medication discontinuation clinical pathway designed to reduce polypharmacy on mean number of medications and patterns of discontinuation compared to usual practice?	Reduction in mean number of medications	Mean number of medications (primary outcome)	*T*_0_, *T*_6_	Linear regression
		Proportion of participants with successful reduction in medication number or dose	*T*_6_	Logistic regression
		Composite variable of mean number of medication discontinuations and/or dose reductions	*T*_6_	Linear regression
What is the effect of a structured medication discontinuation clinical pathway designed to reduce polypharmacy on patient quality of life, cognition, mobility-related fatigue, nutritional status, physical function capacity, pain, sleep, patient enablement, medication self-efficacy, medication confusion, grip strength, falls and adverse events, and hospital admissions compared to usual practice?	Improved disease and treatment burden, quality of life, cognition, fatigue, nutritional status, physical function capacity and ability, pain, sleep, patient enablement, medication self-efficacy and lower/fewer falls, healthcare utilization, and adverse events will be reported in the intervention arm compared to the control arm at 6-months	Disease burden	*T*_0_, *T*_6_	Linear regression
		Treatment burden	*T*_0_, *T*_6_	Linear regression
		Quality of life	*T*_0_, *T*_6_	Linear regression for all continuous outcomes, Logistic regression for Categorical outcomes and Count data models (e.g., Poisson/negative binomial regression, zero-inflated models) for count outcomes
			*T*_0_, *T*_6_	
		Cognition	*T*_0_, *T*_6_	
		Fatigue	*T*_0_, *T*_6_	
		Nutritional status	*T*_0_, *T*_6_	
		Physical function capacity and ability	*T*_0_, *T*_6_	
			*T*_0_, *T*_6_	
			*T*_0_, *T*_6_	
			*T*_0_, *T*_6_	
		Number of Falls	*T*_0_, *T*_6_	
		Pain	*T*_0_, *T*_6_	
		Sleep	*T*_0_, *T*_6_	
		Patient enablement	*T*_0_, *T*_6_	
		Medication self-efficacy	*T*_0_, *T*_6_	
		Healthcare resource utilization (number of hospitalizations, emergency department visits, primary care visits, proportion of patients with at least one hospitalizations)	*T*_0_, *T*_6_	
			*T*_0_, *T*_6_	
			*T*_0_, *T*_6_	
			*T*_0_, *T*_6_	
		Number of Serious adverse events and beneficial withdrawal	*T*_1_, *T*_3_, *T*_6_	
What is the cost-effectiveness of the structured medication discontinuation clinical pathway designed to reduce polypharmacy?	Not applicable	Cost per QALY	*T*_6_	Cost utility analysis
What is the experience of patients as they go through a structured medication discontinuation clinical pathway designed to reduce polypharmacy?	Not applicable	Lived experience with deprescribing process	*T*_6_	Descriptive analysis of Semi-structured interview/patient diaries
		Satisfaction with the intervention (5-point Likert scale)	*T*_6_	Descriptive statistics (M, SD)
		Satisfaction with care around medications (5-point Likert scale)	*T*_0_, *T*_6_	Linear regression
		Strengths and weaknesses of intervention	*T*_6_	Descriptive analysis
What are the experiences of the pharmacist and family physician of managing patients through the deprescribing process?	Not applicable	Lived experience with deprescribing process	*T*_6_	Thematic analysis of semi-structured interviews/field notes
		Confidence in medication discontinuation (5-point Likert scale)	*T*_0_, *T*_6_	Linear regression
		Five best/worst aspects of intervention	*T*_6_	Descriptive analysis
		Implementation processes	Early/late implementation	Descriptive analysis

*T*_*0*_ baseline, *T*_*3*_ month 3, *T*_*6*_ month 6

### Sample size

Sample size calculations for the RCT were performed by the team biostatistician (LT). We used data from our feasibility study to estimate sample size: mean number of medications of 7.7, a post-intervention reduction in mean (standard deviation) of 4.2 (± 2.5). There was consensus from the expert international polypharmacy advisory group that a mean reduction of 2 medications is clinically important [42].

A sample size of at least 160 per group is sufficient to detect a difference in mean number of medications of 2, assuming a starting mean of 7 and a static control group (power set at 80%, significance level 5%). It will also allow detection of an absolute difference in the proportion of patients with drug-related side effects of 15% (10% versus 25%) and provides adequate power for subgroup analysis for the primary outcome if proportions are 40% or more. Allowance has been made for 10% attrition; therefore, the final minimum recruitment target is 180 per group (total *N* = 360).

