### Allocation and randomization

Patients will be randomly allocated 1:1 to either the intervention or control group using an internet accessible computerized system [53]. Randomization will be blocked and stratified by site. The randomization sequence will be generated centrally using a computerized system and will be maintained external to the research team. The Biostatistics Unit at St. Joseph’s Healthcare Hamilton will be responsible for generating the sequence.

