### Quantitative data analysis

The analysis and reporting of the results will follow the CONSORT guideline [71]. The process of patient selection and flow throughout the study will be summarized using a flow diagram. The analysis results of patient characteristics and baseline outcome variables (both primary and secondary) will be summarized using descriptive summary measures: expressed as mean (standard deviation) or median (minimum, maximum) for continuous variables depending on the distribution, and the number (percent) for categorical variables [72]. We will adopt an intention-to-treat (ITT) principle as our primary approach to analyze all outcomes and the people doing the analysis will be blind to study group allocation. Assuming data will be missing at random (MAR), we will also use multiple imputation [MI] through chained equations to impute missing data [73]. In total, five datasets will be imputed and pooled effect estimates (odds ratios for categorical outcomes, mean difference for continuous outcomes, and rate ratio for count outcomes) along with 95% confidence intervals and the associated *p* values will be reported. All statistical tests will be two-sided at the 0.05 level of significance. *P* values will be reported to three decimal places with values less than 0.001, reported as < 0.001. We will not adjust this for multiple analyses for secondary outcomes as we are considering them simply as exploratory. The patient will be the unit of analysis. Adopting an ITT principle, we will use linear regression to analyze both primary and secondary continuous outcomes. Analysis will be blinded. For categorical outcomes, we will use logistic regression. Count data models (e.g., Poisson/negative binomial regression, zero-inflated models) will be used to analyze the count outcomes. We will perform pre-specified subgroup analyses by adding an interaction term between intervention groups and the following subgroups: (1) age (≥ 85 versus < 85 years); and (2) frailty (frail versus severely frail, based on Rolfson et al., 2006 [60]). The interaction tests will be completely exploratory in nature and not adjusted for multiple testing. We examined articles in our review of reviews [74] of interventions to address polypharmacy in older adults living with multimorbidity that may have contained sub-analyses for age and frailty. We found one systematic review that contained a sub-analysis for mortality associated with deprescribing intervention subgroup analyses based on age [75]; and concluded there was no effect. Thus, we hypothesize that there will be no significant interaction effects for either sub-analysis. The interaction tests will be exploratory in nature and not adjusted for multiple testing. We will run sensitivity analyses to assess the robustness of the primary results, adopting a per-protocol approach. All analyses will be performed using SAS software 9.4 (Cary, NC).

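### The 160 per group and its 80% power do not follow from the stated inputs: with the only SD given (2.5), a difference of 2 medications needs 26 per group, and 160 gives more than 99.99% power

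*Protocol article*

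**What the plan says.** The Sample size section takes its planning data from the feasibility study: a mean of 7.7 medications and "a post-intervention reduction in mean (standard deviation) of 4.2 (± 2.5"). It records an expert consensus that "a mean reduction of 2 medications is clinically important". It then states: "A sample size of at least 160 per group is sufficient to detect a difference in mean number of medications of 2". This rests on a mean of 7 at the start and no change among controls, and the sentence closes with "power set at 80%, significance level 5"%.

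Two further uses of the same N follow. It would also detect an "absolute difference in the proportion of patients with drug-related side effects of 15% (10% versus 25"%), and it would give adequate power for subgroup analysis of the primary outcome where the proportions are 40% or more. The section does not say that either of these set the size. A 10% attrition allowance brings the target to 180 per group, 360 in total.

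Other inputs come from neighbouring sections. Allocation and randomization: "Patients will be randomly allocated 1:1 to either the intervention or control group". Quantitative data analysis: "All statistical tests will be two-sided at the 0.05 level of significance"; the patient is the unit of analysis, and the primary outcome is analysed by linear regression. The article states no other SD, no design effect and no subgroup effect size.

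**The concern.** A reader who puts the stated SD, difference, power and significance level into the usual formula gets a sample size about six times smaller than the one in the text. Either 80% is not the power of the design, or the 160 came from a different SD or a different target that the section does not name.

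What is at stake is the account of the design. The power statement is the published justification for enrolling 360 older patients, and it will be cited when the result is interpreted. As written, it suggests that the trial can only just detect the clinically important difference. On the stated SD it can detect differences well under half that size. A related gap is that a power claim is made for a side-effect proportion that cannot be matched by name to a row of the analysis table.

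**Working it through.** **Inputs.** Difference 2; SD 2.5; power 80%; significance level 5% (all from Sample size). Two-sided tests and patient as unit of analysis (Quantitative data analysis). 1:1 allocation (Allocation and randomization). The SD of 2.5 describes the reduction in medications in the feasibility study. It is used here because it is the only one given.

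**1. The plan's own figure.** Normal approximation, per group:

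n = 2 × (1.960 + 0.842)² × (SD/difference)² = 2 × 7.849 × (2.5/2)² = 24.5, so 25.

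The t-test solution is 25.5, so 26. The stated 160 is not reproduced: 160/26 = 6.2.

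**2. Variants for the primary comparison (difference 2).**

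| Variant | n per group |
|---|---|
| SD 2.5, one-sided, 80% power | 20 |
| SD 2.5, two-sided, 90% power | 33 |
| SD 2.5, two-sided, 95% power | 41 |
| SD 2.5, two-sided, 99% power | 58 |
| Poisson variance, means 7 and 5, 80% power | 24 |

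None comes near 160.

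**3. What 160 per group delivers.** The standard error of the difference is SD × √(2/160) = SD × 0.1118.

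- SD 2.5: SE = 0.2795, and 2/0.2795 = 7.16. Power for 2 is 0.9999999.
- Difference detectable with 80% power: 2.802 × 0.2795 = 0.78 (0.79 by the t-test).
- SD needed for 160 to be the 80%-power answer: 2/(2.802 × 0.1118) = 6.39 (6.37 by the t-test), so about 6.4.

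**4. Sensitivity to the SD.** SDs other than 2.5 are assumptions (t-test results, two-sided 5%).

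| SD | n per group for 2 at 80% power | Power for 2 at 160 | Difference with 80% power at 160 |
|---|---|---|---|
| 2.5 | 26 | >99.99% | 0.79 |
| 3 | 37 | >99.99% | 0.94 |
| 3.54 (2.5 × √2) | 51 | 99.9% | 1.11 |
| 4 | 64 | 99.4% | 1.26 |
| 5 | 100 | 94.6% | 1.57 |

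**5. Could the subgroup clause have set 160?** Forty percent of 160 is 64 per group. At SD 2.5, 64 per group has 99.4% power for a difference of 2, so 26/0.4 = 65 per group overall would have been enough. At an assumed SD of 4, a difference of 2 needs 64 per group, and 64/0.4 = 160. That is an exact match, but it rests on an SD that the article does not state.

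**6. Could the side-effect clause have set 160?** For 10% versus 25%, the mean proportion is 0.175:

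n = [1.960 × √(2 × 0.175 × 0.825) + 0.842 × √(0.10 × 0.90 + 0.25 × 0.75)]² / 0.15² = (1.053 + 0.443)² / 0.0225, so 100 per group (113 with continuity correction).

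At 95% power it is 164 (177 corrected). Power at 160 per group is about 94%.

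**7. Attrition.** 160/0.9 = 177.8, so 178. The target of 180 is consistent.

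**8. Table 1.** The nearest row to the side-effect claim counts serious adverse events and beneficial withdrawal. No row is named for the proportion of patients with drug-related side effects.

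**The case against.** The best defence has four parts.

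*The text says sufficient, not necessary.* This stands as far as it goes: 160 per group is more than enough for a difference of 2. An N serving three aims will also exceed what the easiest aim needs. But the same sentence ties the 160 to power set at 80% for that difference, and 80% is not its power.

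*The 2.5 may not be the design SD.* It belongs to a reduction seen in a feasibility study, and the planners used a starting mean of 7 rather than the observed 7.7. The comparison SD may well be larger. The table in the working allows for this. At SD 4, which gives 160 through the 40% subgroup, the power for the main comparison is still about 99%. Only an SD near 6.4 restores 80%, and that is hard to believe beside an assumed mean of 7 in patients who must take at least 5 medications. So the defence offers a plausible origin for 160 but does not rescue the stated power.

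*The side-effect sentence is not wrong.* This stands. The 80% bracket closes the sentence before it, and 94% power does allow detection of 10% versus 25%. A reader might also infer from Table 1 that side effects would never be analysed, and the article does not support that. Adverse events, harms and beneficial withdrawal effects says that new or worsening side effects are collected by solicited inquiry and that all harms will be reported; Check-in data collection adds scheduled telephone calls; and the second hypothesis in Table 1 names adverse events between arms. What remains is only that the powered proportion has no row of its own. Additional File 4, which describes the outcomes and their link to the analysis, is not shown.

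*The result will not be judged on significance alone.* This also stands. At SD 2.5, an observed difference of about 0.55 (1.96 × 0.2795) reaches p < 0.05, and a reader might infer that the trial cannot separate a trivial effect from an important one. But Quantitative data analysis commits to mean differences with 95% confidence intervals, and the important difference of 2 is stated, so the two can be compared.

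**Conclusion.** The point holds as an arithmetic and reporting fault. On the article's own inputs, a difference of 2 at 80% power needs 26 per group. At 160 per group, power for 2 exceeds 99.99%, and 80% power is reached at about 0.8 medications. If the true SD is 4, these become about 99% and 1.26. An SD of about 6.4 would be needed for the sentence to be right.

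A reader might take the mismatch as a sign that the trial is too small, or that its inference is compromised. Neither follows. The discrepancy is towards excess power; type I error, bias and the primary estimate are unaffected, and the attrition step is correct. Severity is therefore minor to moderate.

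The conclusion assumes a two-group comparison of means with the patient as unit, and no design effect, since none is stated. A design effect of about 6.2 would be needed to explain 160 at SD 2.5.

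**What to change.** Keep N = 360 and rewrite the Sample size paragraph so that it gives:

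- the SD assumed for the between-group comparison and its source;
- the criterion that actually set 160 per group; if this was the 40% subgroup, its assumed SD and effect size;
- the true power for the primary comparison: at SD 2.5, more than 99.99% for a difference of 2 and 80% for about 0.8, or the matching figures if another SD was used;
- for the side-effect comparison, about 94% power at 160 per group for 10% versus 25%.

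Then either add the proportion of patients with drug-related side effects to Table 1, with logistic regression as for other categorical outcomes, or remove the power claim.

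Stating that the 95% confidence interval for the primary outcome will be read against 2 medications would be a sensible addition to the reporting. It is optional and does not correct an error.

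The cost is one reworded paragraph and one table row. Enrolment and data collection do not change.

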### Quantitative data analysis

The analysis and reporting of the results will follow the CONSORT guideline [71]. The process of patient selection and flow throughout the study will be summarized using a flow diagram. The analysis results of patient characteristics and baseline outcome variables (both primary and secondary) will be summarized using descriptive summary measures: expressed as mean (standard deviation) or median (minimum, maximum) for continuous variables depending on the distribution, and the number (percent) for categorical variables [72]. We will adopt an intention-to-treat (ITT) principle as our primary approach to analyze all outcomes and the people doing the analysis will be blind to study group allocation. Assuming data will be missing at random (MAR), we will also use multiple imputation [MI] through chained equations to impute missing data [73]. In total, five datasets will be imputed and pooled effect estimates (odds ratios for categorical outcomes, mean difference for continuous outcomes, and rate ratio for count outcomes) along with 95% confidence intervals and the associated *p* values will be reported. All statistical tests will be two-sided at the 0.05 level of significance. *P* values will be reported to three decimal places with values less than 0.001, reported as < 0.001. We will not adjust this for multiple analyses for secondary outcomes as we are considering them simply as exploratory. The patient will be the unit of analysis. Adopting an ITT principle, we will use linear regression to analyze both primary and secondary continuous outcomes. Analysis will be blinded. For categorical outcomes, we will use logistic regression. Count data models (e.g., Poisson/negative binomial regression, zero-inflated models) will be used to analyze the count outcomes. We will perform pre-specified subgroup analyses by adding an interaction term between intervention groups and the following subgroups: (1) age (≥ 85 versus < 85 years); and (2) frailty (frail versus severely frail, based on Rolfson et al., 2006 [60]). The interaction tests will be completely exploratory in nature and not adjusted for multiple testing. We examined articles in our review of reviews [74] of interventions to address polypharmacy in older adults living with multimorbidity that may have contained sub-analyses for age and frailty. We found one systematic review that contained a sub-analysis for mortality associated with deprescribing intervention subgroup analyses based on age [75]; and concluded there was no effect. Thus, we hypothesize that there will be no significant interaction effects for either sub-analysis. The interaction tests will be exploratory in nature and not adjusted for multiple testing. We will run sensitivity analyses to assess the robustness of the primary results, adopting a per-protocol approach. All analyses will be performed using SAS software 9.4 (Cary, NC).

We aim to book the family physician’s appointment within 1 week with a maximum of 2 weeks from the pharmacist appointment but acknowledge this may be difficult due to busy physician schedules or patient commitment changes. We aim to perform another sensitivity analysis to account for these differences in the timeline that may occur through linear regression.

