### Loss to follow-up

We conservatively anticipate the loss to follow-up rate to be a maximum of 10%. Our experience in a discontinuation RCT of antidepressants in primary care showed only a 4% loss to follow-up over 18 months [80], and our feasibility studies in the same age group showed a loss to follow-up of less than 8%. Our TAPER feasibility RCT showed loss to follow-up of only 3 patients. We found regular contact, multiple alternate contact details, and a measured informed consent process, particularly ensuring participants are clearly able to be available for follow-up, are helpful in minimizing such losses. In our feasibility study, we found it unhelpful to recruit participants during the “snowbird” period in winter who were traveling outside of Canada for an extended time as many older Canadians do. Perceived insurance restrictions mean they are not willing to change their medication in the period prior to leaving. The participants lost to follow-up will be classified as lost to follow-up due to an inability to contact, elected to no longer be part of any further follow-up (withdrawal of consent), or unable to participate because of ill health. In cases where participants who are lost to follow-up do not explicitly withdraw consent, medication and health care utilization data will still be collected from patient charts via chart audit where possible.

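### With only five imputed datasets, a pooled p value near 0.05 depends noticeably on the random seed; raising the number to 50 is a free improvement

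*Protocol article*

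**What the plan says.** Quantitative data analysis assumes data missing at random and states that "we will also use multiple imputation [MI] through chained equations to impute missing data". It then sets the number: "In total, five datasets will be imputed and pooled effect estimates", together with 95% confidence intervals and p values, are to be reported for categorical, continuous and count outcomes. The same section says "All statistical tests will be two-sided at the 0.05 level of significance" and that p "values will be reported to three decimal places". It calls the secondary outcomes and the subgroup interaction tests exploratory and leaves them unadjusted for multiplicity. The article gives no reason for five and no rule for raising it.

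Loss to follow-up sets the planned scale of missingness: "We conservatively anticipate the loss to follow-up rate to be a maximum of 10" per cent. It cites lower earlier experience, including that "our feasibility studies in the same age group showed a loss to follow-up of less than 8" per cent. For lost participants who do not explicitly withdraw consent, "medication and health care utilization data will still be collected from patient charts via chart audit where possible".

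**The concern.** Multiple imputation draws random values, so two analysts with the same data and model but different seeds get different pooled results. The size of that difference depends on the number of imputations, m, and on the FMI. Relative efficiency, the usual argument for a small m, describes the average loss of precision. It does not tell a reader directly how far one reported p value would move on a rerun.

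At stake is the reading of results close to 0.05. Table 1 lists many health outcomes, such as quality of life, cognition, fatigue, physical function, pain, sleep, enablement and self-efficacy. They bear on the question raised in the Discussion, whether the harms associated with polypharmacy are reversible. The chart audit covers medications and health care use only, so for lost participants the patient-reported and performance measures would rest on imputation.

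**Working it through.** The figure of five is a stated choice with no derivation, so there is nothing to reproduce. The check asks how much a pooled p value varies over seeds.

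**Inputs from the protocol article.** m = 5; two-sided 0.05; loss of at most 10%; 180 recruited and 160 analysed per group; planned difference of 2 medications; SD 2.5 (Sample size).

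**Assumptions not in the article.** FMI of 4% to 10%, taking it as roughly the share of missing values. It could be lower if baseline predicts the outcome well, or higher if further items are missing among those followed.

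**Step 1: noise in the pooled estimate.** Scale the total variance under infinite imputations to 1, so that the between-imputation variance is B = FMI and the within-imputation variance is W = 1 − FMI. The Monte Carlo SD of the pooled estimate, in units of its standard error, is √(FMI/m):
- FMI 10%, m = 5: √(0.10/5) = 0.141
- FMI 4%, m = 5: √(0.04/5) = 0.089
- FMI 10%, m = 50: √(0.10/50) = 0.045

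Relative efficiency is 1/(1 + FMI/m). At FMI 10% and m = 5 it is 1/1.02 = 0.980, a 2% loss.

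**Step 2: spread of the p value.** For each seed:
- draw the pooled estimate Q from N(1.96, FMI/m);
- draw the between-imputation variance b = FMI × χ²(m−1)/(m−1);
- form T = W + (1 + 1/m)b;
- refer |Q|/√T to a t distribution with Barnard-Rubin degrees of freedom (complete-data df 357 = 360 − 3).

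The value 1.96 corresponds to p = 0.050 without imputation noise. Central 95% ranges of p over seeds:

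| FMI | m = 5 | m = 20 | m = 50 |
|---|---|---|---|
| 4% | 0.033-0.079 | 0.041-0.063 | 0.044-0.058 |
| 10% | 0.025-0.107 | 0.036-0.073 | 0.041-0.064 |

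**Step 3: source of the spread (FMI 10%, m = 5).** With only the noise in the pooled estimate, the range is 0.028-0.098. With only the noise from estimating b on five values, it is about 0.04-0.08. The first source dominates.

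**Step 4: chance of landing on the other side of 0.05 (FMI 10%).**

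| p without imputation noise | m = 5 | m = 50 |
|---|---|---|
| 0.03 | about 15% | about 0% |
| 0.04 | about 35% | about 5% |
| 0.06 | about 25% | about 3% |
| 0.07 | about 13% | about 0% |

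**Step 5: cross-check on simulated data.** One fixed dataset was imputed repeatedly: 180 per arm, SD 2.5, baseline correlation 0.6, 10% missing completely at random, baseline-adjusted linear regression. With 1,500 seeds at m = 5, the range was 0.024-0.106 and the Monte Carlo SD was 0.143 of the standard error, in agreement with steps 1 and 2. A p of 0.03 turned non-significant in 13% of seeds.

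**Step 6: primary outcome.** With 160 per group, SE = 2.5 × √(2/160) = 0.28 and t = 2/0.28 ≈ 7.2. A shift of two Monte Carlo SDs, 2 × 0.14 = 0.28 on the t scale, changes nothing.

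**The case against.** The strongest objection is that the plan is valid as written. Rubin's rules carry the (1 + 1/m) term and a t reference, so the finite number of imputations is already in the interval and p value. Under the null at m = 5, simulated type I error is about 5% at FMI 4% and at FMI 10%. This stands. A reader might infer from the seed dependence that five imputations bias the tests or inflate false positives, and that inference would be wrong.

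A second objection is that little rests on the affected results: the secondary outcomes and interaction tests are declared exploratory, and the primary outcome is safe at the planned effect. This also stands and sets the severity. It does not remove the point, because the pooled p values will still be reported against 0.05.

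Other tempting extensions are not supported:
- **Larger FMI.** A value such as 30% would give far wider ranges, but it lies well above the planned maximum loss of 10%.
- **Mechanism.** The instability should not be put down mainly to estimating the between-imputation variance from five values; step 3 shows that this is the smaller part.
- **Number of outcomes.** Not every secondary row of Table 1 is exposed, since the health care utilization rows can be partly recovered by chart audit. That the remaining outcomes will have more missing data is an inference; the article does not say so.
- **Three decimals.** This is a reporting format and makes no claim of precision.
- **Seed.** Its absence is no finding, as it is commonly left to an analysis plan, and none is shown here.
- **Role of imputation.** The text says imputation will be used also, so it may accompany another analysis and need not be the sole basis for each outcome.

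**Conclusion.** The point holds as a free improvement of the lowest severity, and it does not show an error in the plan. At m = 5 and FMI 10%, imputation noise is about 0.14 of a standard error, enough to move a p of 0.050 anywhere from 0.025 to 0.107 by choice of seed; at FMI 4% the range is 0.033-0.079. Fifty imputations narrow these to 0.041-0.064 and 0.044-0.058. Any finite m leaves some band around 0.05, and five leaves a wide one.

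The size rests on the assumed FMI of 4% to 10% and applies only to results already near the threshold. The primary conclusion would be touched only if the observed effect fell far below the planned 2 medications.

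**What to change.** In Quantitative data analysis, replace five datasets with at least 50 datasets. A floor of 20 would be weaker: at FMI 10% it still leaves 0.036-0.073 for a p of 0.050. With 360 participants the cost is negligible computing time, and the estimand, the missing-at-random assumption, the imputation model and the sample size are unchanged.

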### Data collection

#### Patient characteristics

Patient characteristics that include age, gender, household income, ethnicity, and education will be collected at baseline. Also, a measure of comorbidity [58], medication risk [59], frailty [60], and beliefs about medicines [61] will be completed. Patient preferences, priorities, and goals are recorded as part of the clinical intervention.

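### The exploratory treatment-by-age interaction is tested only as a split at 85, which loses much of the information on a gradual age effect and makes a non-significant result weak evidence

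*Protocol article*

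**What the plan says.** Under Quantitative data analysis the article states: "We will perform pre-specified subgroup analyses by adding an interaction term between intervention groups and the following subgroups". The first of the two subgroups is given as "age (≥ 85 versus < 85 years"; the second is frailty. No analysis with age on a continuous scale is described. The same section labels the tests: "The interaction tests will be completely exploratory in nature and not adjusted for multiple testing". It then sets out an expectation: "Thus, we hypothesize that there will be no significant interaction effects for either sub-analysis".

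Under Patient characteristics: "Patient characteristics that include age, gender, household income, ethnicity, and education will be collected at baseline". The article does not say whether age is held in years or in bands. Entry at 70 together with a cut at 85 makes years a reasonable inference. The Participants section sets a lower age limit of 70 and no upper limit.

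Under Sample size, the planned number "provides adequate power for subgroup analysis for the primary outcome if proportions are 40% or more". The article does not say what share of participants is expected to be 85 or older.

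**The concern.** The split treats everyone from 70 to 84 as the same and places the whole test on the contrast with the upper tail of the sample. If the benefit of TAPER weakens or strengthens steadily with age, the variation within each group is ignored and the test loses power. Because the plan expects non-significance, a test with low power will tend to agree with that expectation whether or not it is true.

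At stake is one of the only two pre-specified questions about who benefits: whether TAPER works equally well in the oldest patients. The primary comparison is not at stake.

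**Working it through.** **The plan's own figures.** The article gives no power or precision for the age interaction. Its only related figure is 160 per group, described as "sufficient to detect a difference in mean number of medications of 2", with the feasibility result "a post-intervention reduction in mean (standard deviation) of 4.2 (± 2.5".
- With a difference of 2, SD 2.5, two-sided 5% and 80% power: n = 2 × (1.960 + 0.842)² × 2.5² / 2² = 24.5, so 25 per group, not 160.
- The SD at which 160 per group gives exactly 80% power is 2 / (2.802 × √(2/160)) = 6.4.

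That mismatch is a separate matter, but it means power should be shown for both SDs.

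**Inputs.** N = 320 analysed (2 × 160); 1:1 allocation; two-sided 5%; SD 2.5 or 6.4. The age distribution is assumed.

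**Formulas.** Let p be the share aged 85 or more, s the SD of age, g the gap between the mean ages of the two groups, and c = 2 × SD / √N. At SD 2.5, c = 5 / √320 = 0.2795.
- Information kept by the split, for a linear modifier: r² = p(1 − p)g² / s².
- Standard error with the split: c / √(p(1 − p)).
- Standard error with continuous age, scaled to the same gap: c × g / s.
- Power for a gap d: Φ(d / SE − 1.96).

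**Worked case.** Truncated normal (77, 6) on 70 to 100: p = 0.104, s = 4.94, g = 10.49.
- r² = 0.0932 × 110.0 / 24.4 = 0.42.
- SE = 0.2795 / 0.3053 = 0.92 with the split, and 0.2795 × 10.49 / 4.94 = 0.59 with continuous age.
- Power for d = 1.5 is 37% and 71%.

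**Four assumed age distributions (70 to 100), linear modifier, d = 1.5 medications.**

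| Age distribution | Share ≥85 | Information kept | Power, SD 2.5: split / continuous | Power, SD 6.4: split / continuous |
|---|---|---|---|---|
| 70 + exponential(6) | 7.6% | 53% | 30% / 50% | 9% / 12% |
| 70 + exponential(8) | 13% | 62% | 45% / 64% | 11% / 15% |
| Truncated normal(77, 6) | 10% | 42% | 37% / 71% | 10% / 17% |
| Truncated normal(80, 6) | 21% | 55% | 59% / 84% | 14% / 21% |

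The gain from continuous age is 19 to 34 points at SD 2.5 and about 3 to 7 points at SD 6.4. The information kept does not depend on the SD.

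For a gap of 2 medications at SD 2.5, which would mean complete loss of the target effect in the oldest group, power is 47%, 68%, 59% and 83% with the split. It is 74%, 87%, 92% and 98% with continuous age.

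**Wider range.** Over truncated-normal, exponential, gamma and uniform ages from 70, the loss is 31 to 65% when about 7 to 25% are aged 85 or more, and 25 to 76% over everything tried. Expressed as a slope (SD 2.5, same 7 to 25% range):
- 1 medication per decade: power 16 to 63% with the split, 36 to 79% with continuous age.
- 2 medications per decade: 47% to nearly 100% with the split, 89% to nearly 100% with continuous age.

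**If the effect truly steps at 85.** The linear term then has power Φ(d√(p(1 − p)) × r / c − 1.96). For a 1.5-medication step at SD 2.5, replacing the split by a linear term lowers power in all four cases: 30% to 18%, 45% to 30%, 37% to 19%, and 59% to 37%.

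**The case against.** The plan twice calls these tests exploratory. Two pre-specified categories compared through an interaction term is conventional practice, and nothing in the article is contradicted. This stands, and it limits the priority.

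A reader might infer that the plan will treat a non-significant test as proof that age does not matter. The article states no such rule. It records an expectation based on an earlier review, and it makes a general commitment to report effect estimates with 95% confidence intervals, although it does not name the interaction term there. What can fairly be said is that the expectation is worded in terms of significance, and non-significance on this scale would support it only weakly.

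A reader might also infer a fixed loss, or that the split would miss any age effect. Neither follows. The loss depends on an age distribution that the article does not give, and a steep gradient would often be detected even with the split.

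Continuous age is not a complete cure. For a 1.5-medication gap it reaches 80% power in only one of the four cases, and at SD 6.4 neither test is informative. It also does worse than the split if the effect really steps at 85. These points stand, and they are why the split estimate should be kept beside the continuous test. Finally, the reason for choosing 85 may be given in a document not shown, so its absence is not held against the plan.

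**Conclusion.** The concern holds in a limited form. For a graded age effect, the test as specified uses clearly less information than the trial will have: about 30 to 65% is lost if 7 to 25% of participants are 85 or older. Under SD 2.5 and a linear modifier, that means power of roughly 30 to 59% where 50 to 84% is available. The conclusion rests on assumed age distributions, on linearity and on age being held in years; the size of the power gain also rests on the SD. It does not show that the plan will misread a null result, and it does not touch the primary analysis. This is a low to moderate priority improvement to an exploratory analysis.

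**What to change.** In Quantitative data analysis:
- Make treatment × continuous age the main exploratory age-interaction test, in the same linear model. Use a linear term, or a spline if non-linearity is a concern.
- Report its coefficient with a 95% confidence interval, and the model-based treatment effect at a few chosen ages.
- Keep the ≥85 versus <85 interaction estimate with its confidence interval alongside, to cover a true step at 85.
- Replace the expectation of non-significance with a statement that conclusions about age rest on the estimates and intervals, and that a non-significant test will not be taken to show absence of effect modification.

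The cost is a few sentences of analysis wording, with no new data, visits or participants. The one statistical cost is lower power of the linear term under a true step (about 30% against 45% for a 1.5-medication step with 13% aged 85 or more, SD 2.5), which the retained split estimate makes visible.
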